## 6.2 CONCOMITANT THERAPY

There is no specified 'per-protocol' concomitant medication or treatment. Any drugs other than those listed in section 6.3.2 are allowed, and should be administered, as necessary for the treatment of the patient. Only concomitant cardiovascular treatments, such as other catecholamines, hydrocortisone or others, should be documented on the appropriate eCRF. Fluid boluses are considered also cardiovascular treatment and should be recorded on the eCRF.

All allowed medications that have been started before screening may be continued during the study. Medications for treatment of emerging illnesses that arise after screening will be allowed. The medication and the condition must be documented on the adverse event page of the eCRF (when applicable, please refer to the assessment of safety section of the protocol). For any concomitant therapy given as a treatment for a new condition or a worsening of an existing condition, the condition must be documented on the adverse event page of the eCRF (when applicable, please refer to the assessment of safety section of the protocol).

---

### 6.2.1 Rescue Treatment

A change in treatment strategy using rescue treatments is allowed if no clinical response to the study intervention is considered by the attending physician, when the

- MABP < GA-5 mmHg
- and one or more of the following:
- SVC flow < 51 ml/kg/min (after 1 hour)
  - Rising serum lactate
  - Base excess being more negative
  - CRT ≥ 4sec

Rescue treatments include:

- Additional fluid bolus
- vasopressor-inotrope therapy, apart from commercial dobutamine
- corticosteroids
- other treatment administered to treat haemodynamic insufficiency

When rescue treatment is needed physicians will be encouraged to consider up-titration option first, to try to maintain the infant in the study drug only treatment corridor as long as possible, if it is the best option for the infant. Rescue treatment will not include commercial dobutamine.

---

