A significant proportion of babies born at less than 32 weeks' gestation require cardiovascular treatment in the hours after birth, even in the absence of identifiable pathologies. This indicates that haemodynamic insufficiency in this age group can be related to an immature adaptation to birth.

The conventional approach to infants at risk of haemodynamic insufficiency is to monitor the babies using clinical signs, mostly blood pressure. However, blood pressure is a poor surrogate of systemic and organ (including brain) blood flow during the transitional period from intra- to extra- uterine life. This state is characterised by increased peripheral vascular resistance and therefore increased afterload, which may cause myocardial dysfunction and impaired blood flow in spite of 'normal' central blood pressure.

We propose an alternative approach, which focuses on evidence of blood flow distribution and poor perfusion. One pilot, randomised placebo-controlled trial on dobutamine for early haemodynamic insufficiency, defined as low SVC flow ( $<41$  ml/kg/min), conducted in infants below 31 completed weeks' gestation, has been recently published (11). Eligible infants were prospectively evaluated for several parameters of circulatory impairment from birth, and randomised to dobutamine or placebo in case of low SVC flow within the first 24 hours. An analysis in retrospect of the non-randomised infants, looking at biomarkers that would qualify as a criterion for inclusion of patients in a future phase III clinical trial to demonstrate efficacy for cardiovascular treatment in the indication under investigation, found SVC flow  $<51$  ml/kg/min, mean arterial blood pressure (MABP)  $<$  gestational age (GA)-5 mmHg, and lactate above 4 mmol/L as the biomarkers that better predicted combined adverse outcome (death or severe intracranial haemorrhage or white matter damage)(12). The use of a combination of biomarkers that have been proven to be as good predictors for adverse outcome, will better define the population at risk of end-organ damage due to abnormal blood flow distribution that eventually would benefit of cardiovascular treatment.

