## 5 STUDY POPULATION

### 5.1 INCLUSION CRITERIA

Infants are eligible to be included in the study only if they meet **all** the following criteria:

- Born up to 32(+6) weeks gestation
- Presence of haemodynamic insufficiency, defined as SVC flow <51 ml/kg/min.
- Provision of signed and dated informed consent form by father/mother or legally designated representative, which can be given antenatally as described in section 5.4.

Three notes of caution are necessary with respect to inclusion of infants into this trial:

- The treating physician needs to be at “clinical” equipoise on providing the proposed trial of dobutamine-treatment to the infant, which can be justified as explained in section 2.1 above.
- To avoid over treatment, the treating physician needs to fully understand the determinant of the pathophysiology of circulatory impairment and use clinical judgment to decide treatment. For example, during severe congenital anaemia a baby meeting the inclusion criteria will not be included and will instead get the required blood volume replacement first; and only afterwards could be considered for inclusion if still eligible.
- Deferred informed consent and prior informed assent (opt-out with enrollment as default) are plausible in this condition because it is in accord with Article 35 of the Regulation of the European Union on Clinical Trials (Regulations (EU) no536/2014), that states: Informed consent to participate in a clinical trial may be obtained, and information on the clinical trial may be given, after the decision to include the subject in the trial, provided that this decision is taken at the time of the first intervention on the subject, in accordance with the protocol for that clinical trial and that all the following conditions are fulfilled:
  - Urgency of the situation, caused by a sudden life-threatening or other serious medical condition
  - Scientific grounds to expect that participation of the subject in the trial will have the potential to produce a direct clinically relevant benefit for the subject resulting in a measurable health-related improvement or in the diagnosis of its condition

- It is not possible within the therapeutic window to supply all prior information to and obtain prior informed consent from his/her legally designated representative
- The investigator certifies that he or she is not aware of any objections to participate in the clinical trial previously expressed by the legally designated representative

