#### 6.1.2 Dosing and Administration

The study medication for infusion will be prepared and administered with strict standardisation of the administration system to minimise systematic errors due to differences in infusion set-ups. This will ensure the precise time at which dobutamine enters the body can be recorded (t0).

The infant's treatment will be guided by the responsible physician who will use the study medication under the premise of keeping a minimum time of 60 minutes from the effective infusion of dobutamine (t0) for PD assessment.

Once the primary PD variable has been assessed further management will be at the discretion of the attending physician. Therefore, if there is no PD response according to protocol with the allocated starting dose, or even if there were, the clinical situation of the patient so recommends it, the responsible physician decide on further treatment (Rescue treatment in section 6.2.1). However, clinicians are encouraged to consider the up-titration to maximum dobutamine dose first, to try to maintain the infant in the study drug as long as possible, if it is the best option for the infant.

Any changes to the treatment strategy will be documented by the responsible physician.

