#### *8.1.1.4 Treatment: PD/PK Assessment Visit*

The patient PD response to the dobutamine treatment should be evaluated at 60 minutes from the start of effective dose infusion, to establish if the treatment success dose has been achieved. Blood sample (1 millilitre) will be taken.

Effective dose infusion is define as the time ( $t_0$ ) when the study medication enters blood stream, which is calculated according to the following equation:

$$t_0 = t_{\text{switch on}} + t_d$$

$$t_d (\text{min}) = (\text{volume (ml)} / \text{velocity (ml/h)}) \times 60 (\text{min/h}),$$

where *volume* refers to the catheter lumen plus the stopcock dead space and *velocity* refers to the summation of the infusion rate of all the infusions coming through the line. Dobutamine infusion should be at the stopcock closest to the catheter entry. Before dobutamine is connected to the stopcock, the whole system (including bionector) will be fed with the dobutamine solution and the pump will be switched on for a few minutes to ensure that no pulling out effect is added at start. The pump will be switched off and the system will be connected to the stopcock. Finally the pump will be switched on and the time will be registered ( $t_{\text{switch on}}$ )

The following criteria will be checked at every patient at the dose evaluation:

- Main response biomarker: SVC flow > 55 ml/kg/min

And other parameters:

- MABP increase by 20% (roughly 4-6 mmHg)
- Decreasing serum lactate levels
- Base excess levels being less negative
- CRT < 4 sec

Throughout the treatment, a series of clinical and biochemical parameters described in sections 8.1.2 below are evaluated and recorded in the eCRF according to the timings given in the section 1.3.

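### A non-responder whose mean blood pressure is not below GA-5 mmHg has rescue open under section 6.1.2 but not under sections 6.2.1 and 6.2.2

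*Protocol*

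**What the plan says.** **Entry and response.** Section 5.1 gives the haemodynamic entry criterion as "Presence of haemodynamic insufficiency, defined as SVC flow <51 ml/kg/min" and lists no blood pressure criterion. Section 8.1.1.4 gives the yardstick for response: "Main response biomarker: SVC flow > 55 ml/kg/min".

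**After the assessment.** Section 6.1.2 says "Once the primary PD variable has been assessed further management will be at the discretion of the attending physician". Its trigger is "if there is no PD response according to protocol with the allocated starting dose", extended to infants who did respond if their condition calls for it. Its action is "the responsible physician decide on further treatment (Rescue treatment in section 6.2.1"). No blood pressure condition is attached. Section 6.1.3 likewise links rescue simply to the absence of a clinical response. For details it refers to a section 6.4.1, which does not appear in the protocol as supplied.

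**The rescue rule itself.** Section 6.2.1 opens with "A change in treatment strategy using rescue treatments is allowed if no clinical response to the study intervention is considered by the attending physician", and the same sentence then adds conditions. The first is "MABP < GA-5 mmHg". It is joined by a written *and* to at least one of four further signs: SVC flow still <51 ml/kg/min after 1 hour, rising lactate, worsening base excess, or capillary refill time of 4 s or more. Commercial dobutamine is excluded from rescue. Section 6.2.2 restricts fluid bolus and vasopressor-inotrope therapy to use as rescue. Sections 6.1.2 and 6.2.1 both encourage up-titration of dobutamine first.

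**The endpoint.** Footnote [B] (synopsis and section 3) treats a switch to any cardiovascular treatment beyond dobutamine, including a further fluid bolus, as loss of acceptable haemodynamic status. It names the need for rescue among the reasons. Section 8.1.1.6 requires at 72 hours that the infant is alive, meets five clinical targets and has received dobutamine alone, at any dose.

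**The concern.** Entry and response are defined by flow, while section 6.2.1 makes low pressure a necessary condition for rescue. Section 2.1.1 itself says that "blood pressure is a poor surrogate of systemic and organ (including brain) blood flow during the transitional period" and allows that flow may be impaired while central pressure looks normal. An infant who enters on low flow, does not respond, and has MABP at or above GA-5 is therefore foreseeable. For that infant the sections give different answers.

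Two things are at stake. The first is a safeguard: section 2.4.3 cites the rescue section among the trial's risk mitigation measures, so it should give one answer for every enrolled infant. The second is the 72-hour secondary endpoint, which counts treatment other than dobutamine as loss of status. Two physicians facing the same infant could follow different sections and generate different outcomes.

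**Working it through.** The check is mainly a comparison of rules, followed by a count from the protocol's planning table.

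**Step 1: a test case run through each section.** Take an infant of 28 weeks, enrolled at SVC flow 45 ml/kg/min with MABP 29 mmHg. At 60 minutes SVC flow is still 45, lactate is rising and capillary refill time is 5 s. The pressure limit in 6.2.1 is 28 − 5 = 23 mmHg.

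| Section | Test | Result |
|---|---|---|
| 5.1 | SVC flow 45 < 51 | eligible |
| 8.1.1.4 | SVC flow 45 is not > 55 | no response |
| 6.1.2 | no PD response | further treatment, labelled rescue, at the physician's discretion |
| 6.1.3 | no clinical response | rescue described without a pressure condition |
| 6.2.1 | MABP 29 is not < 23 | necessary condition not met, although three of the four further signs are present |
| 6.2.2 | bolus and vasopressor-inotrope only as rescue | closed if 6.2.1 is not met |

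Up-titration of dobutamine remains, encouraged by both 6.1.2 and 6.2.1. Section 6.2.1 does not count it as rescue.

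**Step 2: what this does to the 72-hour endpoint.** There are three courses for such an infant:

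- (a) A bolus or another agent is given, relying on 6.1.2. The infant fails the dobutamine-alone condition, whatever its later state.
- (b) The infant stays on up-titrated dobutamine, as 6.2.1 and 6.2.2 imply, and recovers. It can meet every item in 8.1.1.6 and count as a success.
- (c) The infant stays on up-titrated dobutamine and does not recover. It fails on the clinical items.

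Courses (a) and (c) both end in failure. The section followed changes the result only for an infant who would have taken course (b) but was managed under (a).

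**Step 3: the primary endpoint.** An infant with SVC flow not above 55 at 60 minutes is already a non-responder to the allocated dose. Under 6.1.2 the rescue decision comes after that assessment, so it cannot alter that infant's primary result.

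**Step 4: a ceiling on the number.** The table in section 9.1.1 plans 5, 9, 12 and 4 infants at the four lowest doses, with efficacy 45, 70, 80 and 90%.

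- Expected responders: 5 × 0.45 + 9 × 0.70 + 12 × 0.80 + 4 × 0.90 = 2.25 + 6.30 + 9.60 + 3.60 = 21.75.
- Expected non-responders to the allocated dose: 30 − 21.75 = 8.25.
- At the upper ends of the prior ranges (50, 75, 85, 95%): 2.50 + 6.75 + 10.20 + 3.80 = 23.25 responders, so 6.75 non-responders.

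Infants in the conflict are the subset of these with MABP at or above GA-5. The protocol gives no share for them, so the expected number lies anywhere from none to about 8. Infants whose 72-hour outcome changes are a further subset, by Step 2. With 30 infants in the denominator, each moves the 72-hour proportion by 1/30, or 3.3 percentage points. Section 9.1.2 excludes losses of status with another confirmed cause, so the denominator may be somewhat smaller.

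**The case against.** **The pressure term has a stated basis.** Section 2.1.1 names MABP < GA-5 among the biomarkers that best predicted adverse outcome and favours combining biomarkers. This stands: the term is not arbitrary, and nothing here says it should go. It does not settle how 6.1.2 and 6.2.1 fit together.

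**Section 6.2.1 permits; it does not say only.** That is true of its wording. The exclusivity comes from 6.2.2, and only for boluses and vasopressor-inotropes. Section 6.2 also allows other necessary drugs except those listed in a section 6.3.2, which does not appear in the protocol as supplied, so its reach is uncertain. This softens the point but leaves the conflict in place for the two classes that 6.2.2 names.

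**Section 6.1.2 cites 6.2.1 and so is subordinate to it.** On that reading its discretion to rescue has no effect in an infant whose pressure is not low, although it is written to reach even infants who responded. Section 6.1.3 would still describe rescue without the pressure condition.

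**The infant is not left untreated.** Correct. A reader might infer that following 6.2.1 leaves such infants with no option; up-titration is open in both sections.

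Two further inferences are tempting and unsupported. One is that the typical trial infant has normal pressure: section 2.1.1 says only that this may happen and gives no frequency. The other is that SVC flow of 51 to 55 is an unclassified gap. Such an infant is plainly a non-responder, and the other three signs in 6.2.1 can still satisfy its second limb. Different thresholds for success and escalation can be a deliberate choice.

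**Conclusion.** Sections 6.1.2 and 6.1.3 on one side and 6.2.1 with 6.2.2 on the other cannot all be followed for a non-responder with MABP at or above GA-5. The protocol foresees such infants but does not count them. The ceiling is about 8 of 30, resting on the planning efficacies and allocation in section 9.1.1 and taken before any up-titration.

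A reader might infer that the 72-hour outcome of every such infant depends on the section followed. Footnote [B] does not support that: it turns on a change of treatment actually made, and an infant who stays unwell fails either way. The effect is confined to infants who would have recovered on up-titrated dobutamine. Nor does the conflict reach the primary outcome of infants not responding at 60 minutes.

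This should be fixed, because it concerns a safeguard the protocol relies on and one secondary endpoint. It does not undermine the dose-finding result.

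**What to change.** Reconcile sections 6.1.2, 6.1.3, 6.2.1 and 6.2.2 into one rescue rule that gives a single answer for every infant eligible under section 5.1. The rule should say whether the pressure criterion is necessary for rescue, and how it relates to the discretion granted in 6.1.2. The sponsor's clinicians choose the rule; this review takes no position on it.

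Correct the references to sections 6.4.1 and 6.3.2. Tie the need for rescue treatment in footnote [B] to the reconciled rule, so that it means the same in the synopsis, section 3 and section 8.1.1.6.

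The cost is amendment wording. No new procedures, visits or patients are needed.

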### 6.2.2 Precautionary Medications, Treatments and Procedures

- Entacapone: This drug is a selective inhibitor of the catechol-o-metil transferase. Actions and side effects may be increased by dobutamine.
- Beta-blockers: The inotropic effect of dobutamine stems from stimulation of cardiac beta1 receptors, this effect is reversed by concomitant administration of beta-blockers. Dobutamine has been shown to counteract the effect of beta-blocking drugs. In therapeutic doses, dobutamine has mild alpha1- and beta2-agonist properties. Concurrent administration of a non-selective beta-blocker such as propranolol can result in elevated blood pressure, due to alpha-mediated vasoconstriction, and reflex bradycardia. Beta-blockers that also have alpha-blocking effects, such as carvedilol, may cause hypotension during concomitant use of dobutamine due to vasodilation caused by beta2 predominance (see section 4.4 Special warnings and precautions for use).
- Alternative fluid bolus (only allowed as rescue medication)
- Vasopressor-inotrope therapy (only allowed as rescue medication)

### 6.2.3 Prophylactic Medications, Treatments and Procedures

There will not be, per protocol, any prophylactic medication, treatment, or procedure. Overall care of the infant will follow the policies currently in use in the unit.

## 7 STUDY INTERVENTION DISCONTINUATION AND PARTICIPANT DISCONTINUATION/WITHDRAWAL

### 7.1 DISCONTINUATION OF STUDY INTERVENTION

Discontinuation from commercial dobutamine does not mean discontinuation from the study, and remaining study procedures should be completed as indicated by the study protocol. If a clinically significant finding is identified after enrolment, the investigator or qualified designee will determine if any change in participant management is needed. Any new clinically relevant finding will be reported as an adverse event (AE).

The criteria for enrolment must be followed explicitly. If a patient who does not meet enrolment criteria is inadvertently enrolled, that patient is to be discontinued from the study drug but observation should be continued according to the study protocol in order to provide the follow-up data needed for the analysis of the entire intention-to-treat population, to which the patient belongs formally.

In addition, patients will be discontinued from study treatment in the following circumstances:

- a) The investigator decides that the patient should be withdrawn from study treatment. If this decision is made because of a serious AE (SAE), the study drug is to be discontinued, and appropriate measures are to be taken. The Sponsor or its designee is to be notified immediately.
- b) The infant's parent(s)/legal representative, for any reason, requires treatment with another therapeutic agent that has been demonstrated to be effective for treatment of the study indication. In this case, discontinuation from study treatment should occur immediately upon introduction of the new agent.

Investigator decides to withdraw the patient: Patients who discontinue the study drug early will have the Last Treatment Assessment (LTA) Visit procedures performed as shown in the SoA (section 1.3). Discontinuation of study treatment does not necessarily mean that observation in line with the protocol needs to end at this point in time and, unless indicated from the treating physician's opinion, should proceed in line with the study plan.

Legal representative decision: Infant's parents/ legal representative will be asked whether they will consent the infant to remain in the trial for the remaining study- and follow-up assessments and inclusion of his/her already collected data in a database, a registry, or a publication. All efforts will be made to complete and report the observations as thoroughly as possible up to the date of withdrawal. All information should be reported on the applicable CRFs.

Withdrawal of partial consent means that the participant's legal representatives do not wish the participant to take investigational medical products any longer but are still willing to collaborate in providing further data by continuing with the study (i.e., participating in subsequent study visits or procedures and/or provide overall survival information).

### 7.2 PARTICIPANT DISCONTINUATION/WITHDRAWAL FROM THE STUDY

A participant may be withdrawn from the study at any time at the request of his/her parent(s), or may be withdrawn at any time at the discretion of the investigator or sponsor for safety or administrative reasons.

If a participant withdraws from the study, he/she may request destruction of any samples taken and not tested, and the investigator must document this in the site study records.

The Last Treatment Assessment (LTA) Visit data should be collected at the time of study discontinuation and the reason for participant discontinuation or withdrawal from the study will be recorded on the early discontinuation form of the eCRF.

Subjects who sign the informed consent form and are randomized but do not receive the study intervention will be excluded from the Intention-To-Treat (ITT) population and may therefore be replaced. There will be no replacement of subjects who withdraw after they have been enrolled in the study and received at least one dose of study drug.

